#### Participants

2.1.2

Using a within-subject study design, this study will enroll 30 neurologically healthy patients scheduled for elective surgery under GA. The sample size is justified based on feasibility, prior literature, and the within-subject design of the study. Patients will be included if they are aged 18–80 years, comprehend French or English, have an American Society of Anesthesiology (ASA) score of I to III, and are scheduled for major elective surgery (abdominal, gynecologic, urologic, thoracic, or orthopedic) requiring more than 60 min of GA. Patients will be excluded for unstable coronary pathology, heart rhythm disorder, emergency or brain surgery, pregnancy, preoperative hemodynamic failure, substance use disorder (alcohol, drugs, opioids as defined by the DSM-V) in the last 3 months, daily use of opioids in the last 7 days, chronic pain conditions, severe psychiatric pathologies, or epilepsy.

Patients will be contacted by phone within 7 days prior to their surgery by a member of the study team who is not a member of the patient’s treating team. Details of the study will be explained to them, and all questions answered by a member of the study team, who will also verify inclusion/exclusion criteria. The information and consent form, as well as an illustrative document explaining study procedures, will be sent to eligible patients by email. The morning of the surgery, a member of the research team will meet the patients to address any concerns and written informed consent will be obtained.

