#### Procedures for SA1 and SA2 (part 1)

2.2.2

Once anesthesia dosage is stable, BIS values are 40–60, predicted remifentanil Ce is <0.5 ng.mL-1 and the NOL is below 10, in-ear earphones (ER2XR Earphones; Etymotic Research, IL, United States) will be placed in patients’ ears, through which the CLAS auditory stimulation will be provided binaurally. These earphones already provide a 32–45 dB attenuation. To further attenuate ambient sounds in the OR, noise-blocking earmuffs (Peltor Optime 105; 3 M, MN, United States), effective up to 105 dB of ambient noise, will be placed over the earphones. The hd-EEG-CLAS software package will then deliver *in-phase*, *anti-phase*, and Rest (*sham*) stimulation blocks for 3 min each, with 20-s pauses between each stimulation type (10 min total). This interval is considered sufficient to prevent any carryover effects, as CLAS has shown only stimulus-locked effects, and do not persist beyond the targeted slow oscillatory cycles (Ngo et al., 2013; Ngo et al., 2015). Given that anesthetic doses will be stable and no CLAS carryover effect is expected beyond each stimulated wave, no randomization of stimulation blocks will be conducted. Under general anesthesia, cortical dynamics may gradually deepen over time despite stable TCI and by applying *in-phase* stimulation first, we adopt a conservative design that minimizes the risk of falsely attributing time-dependent anesthetic deepening to stimulation effects. Minimal physical contact will be made with the participant, and a minimal noise level will be maintained in the OR throughout the study for optimal isolation of the CLAS effects.

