### EEG pre-processing

3.1

EEG data will be preprocessed using a custom MNE Python script and will be bandpass filtered from 0.1 to 50 Hz. Non-scalp, noisy channels, and channels overlapping with the BIS monitor will be removed. EEG data will be re-referenced to an average reference. Data will then be segmented into the 6 conditions of study: (1) *In-phase*; (2) *Anti-phase*; (3) *sham*; (4) *Pre-Pain*; (5) *Pain*; (6) *Post-Pain*.

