#### Effect of CLAS on *δ*-waves morphology and topography

3.7.1

EEG data will be processed at the level of individual channels to characterize the impact of CLAS on δ-wave morphology and topography using custom Python scripts. Each detected δ-wave will be segmented as a single event (250–10,000 ms duration), and morphology will be quantified by amplitude, slope, transition frequency, density, and power spectral density (Bouchard et al., 2021). These metrics will be compared across conditions (*in-phase*, *anti-phase, sham*) and cortical regions of interest (frontal, central, midline, parietal, temporal, occipital). Descriptive statistics will be computed at both the subject and group level, with comparisons assessed using repeated-measures ANOVA and independent-samples *t*-tests, including age and sex as covariates.

Topographical EEG maps will be generated for canonical frequency bands (delta (0.1–4 Hz), theta (4–8 Hz), alpha (8–13 Hz), beta (13–30 Hz)), and phase-amplitude coupling measures will be calculated to further assess condition-dependent differences in oscillatory dynamics. Topographical mapping will allow testing for regional differences, as frontal predominance of *δ*-waves is a hallmark of both sleep and propofol anesthesia (Murphy et al., 2011; Purdon et al., 2015). To extend beyond scalp measures and as an exploratory aim, source estimation will be performed using standardized head models (Michel and He, 2019). Finally, propagation analyses will be conducted to quantify directionality of δ-wave travel across the cortex, as slow oscillations are known to spread as traveling waves and have been proposed as indices of large-scale cortical communication (Massimini et al., 2004; Tononi and Massimini, 2008).

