#### Association of CLAS with depth of anesthesia

3.7.2

Depth of anesthesia will be evaluated using the BIS index, an EEG-derived index validated for intraoperative monitoring (Connor, 2022; Rampil, 1998). BIS index values will be compared across *in-phase*, *anti-phase*, and *sham* blocks using repeated-measures ANOVA and pairwise paired *t*-tests with Holm–Bonferroni correction, to control for multiple comparisons. To probe the relationship between the BIS index and underlying cortical dynamics, correlation analyses will be run between BIS values and *δ*-wave features (amplitude, slope, spectral power), building on prior evidence that BIS partly reflects the presence and strength of slow oscillatory activity (Akeju and Brown, 2017; Bruhn et al., 2000). To further dissociate oscillatory modulation from global state-dependent spectral changes, the aperiodic (1/f) parametrization will also be extracted for each block and examined in relation to BIS values (Donoghue et al., 2020; Lendner et al., 2020).

The impact of CLAS large-scale neural dynamics during general anesthesia will also be quantified through EEG-derived network measures, including functional connectivity (wPLI, Vinck et al., 2011; dPLI, Stam and Van Straaten, 2012) and graph-theoretical properties (network motifs; degree and direction of frontoparietal connectivity; Lee and Mashour, 2018). We will also investigate the effect of CLAS on EEG microstates in order to characterize the temporal dynamics of whole-brain neuronal network.

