#### CLAS and nociceptive stimulation

3.7.3

Because nociceptive stimulation will be delivered only during *in-phase*, the primary analyses will assess within-subject changes across the *Pre-Pain*, *Pain*, and *Post-Pain* epochs. As a first step, *δ*-wave morphology will be quantified by comparing amplitude, slope, and power spectral density (PSD) across the three conditions, since these features provide sensitive markers of cortical arousal and nociceptive disruption under anesthesia (Bonhomme et al., 2016; Plourde et al., 2006). To dissociate band-limited power changes from broadband spectral shifts that can occur under propofol anesthesia, we will additionally parameterize the aperiodic (1/f-like) component of the EEG power spectrum for each stimulation block. Power spectral density will be estimated per block and channel, and the aperiodic exponent (slope) and offset will be extracted over a predefined frequency range using spectral parameterization methods. These aperiodic parameters will be compared across *in-phase, anti-phase*, and *sham* conditions and, where relevant, included as covariates when interpreting *δ*-band power changes.

The primary analysis of nociceptive reactivity will be changes in the NOL index and time-to-recovery. Secondary analysis will examine changes in mean arterial pressure (MAP), heart rate (HR), and BIS index values. Source localization and propagation analyses will further characterize the cortical generators and spatiotemporal spread of δ-waves during nociception (Massimini et al., 2004; Murphy et al., 2011).

Statistical models will include linear mixed-effects analyses with Condition (*Pre-Pain*, *Pain*, *Post-Pain*) as a fixed factor and age, and sex. *p*-values will be corrected for multiple comparisons using familywise error correction. This design enables testing whether *in-phase* CLAS can preserve *δ*-wave integrity and stabilize autonomic reactivity in the presence of nociceptive input, a key criterion for balanced anesthesia (Garcia-Larrea and Bastuji, 2018).

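### SA1 is analysed by repeated-measures ANOVA and SA3 by a linear mixed model, although both have the same within-patient structure; the primary aim gets the method that cannot use an incomplete patient

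*Protocol article*

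**What the plan says.** All references are to the protocol article.

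- **SA1, the primary aim (3.7.1).** Amplitude, slope, transition frequency, density and power spectral density are compared across in-phase, anti-phase and sham and across six regions, "with comparisons assessed using repeated-measures ANOVA and independent-samples" t-tests. Age and sex are covariates.
- **SA2, BIS (3.7.2).** BIS is compared across the three "blocks using repeated-measures ANOVA and pairwise paired" t-tests, with Holm–Bonferroni correction.
- **SA3 (3.7.3).** "Statistical models will include linear mixed-effects analyses with Condition" (Pre-Pain, Pain, Post-Pain) as a fixed factor, with age and sex.
- **Sample (2.1.2).** "this study will enroll 30 neurologically healthy patients scheduled for elective surgery under GA". The basis given is: "The sample size is justified based on feasibility, prior literature, and the within-subject design of the study".
- **Part 1 session (2.2.2).** "stimulation blocks for 3 min each, with 20-s pauses between each stimulation type (10 min total"), and "no randomization of stimulation blocks will be conducted". In-phase comes first, and sham is listed last.
- **Pre-processing (3.1).** Noisy channels and "channels overlapping with the BIS monitor will be removed". The article describes this step before segmentation into conditions.

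**The concern.** SA1 and SA3 come from the same patients in the same session, and each compares three conditions within a patient. The primary aim nevertheless has the model family that needs every within-patient cell, while a later aim has the one that uses whatever cells exist.

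If a patient lacks the sham block, a classical ANOVA also discards that patient's in-phase and anti-phase data from the omnibus test, although those two blocks form a complete pair. At stake are some precision for the primary aim and an omnibus result that may rest on fewer than the 30 enrolled. The sample-size statement shows no power margin or dropout allowance to absorb this.

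**Working it through.** **Inputs.** From the article: n = 30 (2.1.2), three blocks (2.2.2), six regions (3.7.1). The article gives no alpha, power, effect size, SD or missing rate, so there is no planned figure to reproduce. Assumed here: two-sided alpha 0.05; 80% power at n = 30; compound symmetry with within-patient correlation ρ from 0.5 to 0.9; k = 1 to 3 patients lacking one block.

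**1. Power lost under complete-case analysis.** For a paired t-test with standardised difference d, power comes from the noncentral t distribution with n − 1 degrees of freedom and noncentrality d√n. Setting power to 80% at n = 30 gives d = 0.529. With d held there:

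| Complete patients | Power | Loss (points) |
|---|---|---|
| 30 | 80.0% | – |
| 29 | 78.6% | 1.4 |
| 28 | 77.0% | 3.0 |
| 27 | 75.4% | 4.6 |

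**2. What a mixed model recovers if k patients lack sham.** By generalised least squares, the effective n for in-phase versus sham satisfies

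1/n_eff = w/(30 − k) + (1 − w)/30, with w = (1 + 2ρ)/[2(1 + ρ)].

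- ρ = 0.5: w = 2/3. For k = 3, 0.667/27 + 0.333/30 = 0.0358, so n_eff = 27.9.
- ρ = 0.9: w = 2.8/3.8 = 0.737. For k = 3, 0.737/27 + 0.263/30 = 0.0361, so n_eff = 27.7.

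Complete-case n is 27, so 0.7 to 0.9 of the 3 lost patients are regained, about a quarter to a third. For k = 1, n_eff is 29.3 against 29.

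For in-phase versus anti-phase, the same patients have both blocks, and the mixed model keeps n_eff = 30. Likewise, if anti-phase is the missing block, in-phase versus sham keeps n_eff = 30.

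**3. The random effects matter.** Suppose condition × region is fitted with a random intercept for patient only. Patient-by-condition variation then goes into the pooled residual, and the six regions act as replicates. Let r be the patient-by-condition variance divided by the residual variance. With 30 patients and 3 × 6 cells, the residual has 29 × 17 = 493 degrees of freedom, of which 29 × 2 = 58 are patient-by-condition. With no true effect, the condition F statistic is inflated by about

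(1 + 6r) / {[58(1 + 6r) + 435]/493}.

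The 5% critical value of F(2, 493) is 3.01, and the false-positive rate is about exp(−3.01/inflation):

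| r (assumed) | Inflation | Formula | Simulation |
|---|---|---|---|
| 0.10 | 1.49 | 13% | 14% |
| 0.25 | 2.13 | 24% | 24% |
| 0.50 | 2.96 | 36% | 35% |

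The ANOVA with the patient × condition error term stays near 5%. A mixed model for SA1 therefore needs the patient-by-condition term.

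**The case against.** The strongest reply is that missing-data handling is usually left to an analysis plan, which is not shown. The article states no listwise deletion, no incomplete sessions and no missing rate. That stands, and the loss is therefore conditional. What the article does fix is the model family for each aim, and that choice can be questioned on its own.

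A reader might infer several stronger points that the documents do not support:

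- **Heavy loss over 18 cells.** At an assumed 2% independent loss per cell, 30 × 0.98^18 leaves about 21 patients. Section 3.7.1 does not say that one 3 × 6 ANOVA will be run; separate ANOVAs per region would need three cells each. Section 3.1 describes channel removal before segmentation, so a removed channel is lost in all blocks together. Removal is per channel from a 128-channel net, and nothing suggests that a whole region is emptied. Independent cell loss does not fit this.
- **SA1 and SA3 would rest on different patients because sessions end early.** Part 2 follows completion of Part 1 (2.2.3), so a session stopped before sham also has no SA3 data.
- **BIS suffers equally.** BIS is a secondary outcome without regions, and its paired t-tests already use every patient with the two blocks compared.
- **A mixed model would remove bias from suppressed δ-waves.** If a cell is empty because amplitude was suppressed, missingness depends on the unseen value, and a missing-at-random model does not cure that. The route is also speculative: section 1.2 describes propofol slow oscillations as regular and of high amplitude, and density and power would still have values.
- **The ANOVA wastes data that a mixed model would fully restore.** When sham is missing, most of the in-phase versus sham loss is unavoidable.

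**Conclusion.** The inconsistency is real and unexplained: the same within-patient structure gets two model families, and the primary aim has the one that would drop an incomplete patient from its omnibus test. The consequence is modest. With 1 to 3 of 30 patients lacking a block, power falls by about 1 to 5 points from 80%. A mixed model restores all of any contrast whose two blocks are present, and about a quarter to a third of the in-phase versus sham loss when sham is missing.

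These sizes rest on the assumed number of incomplete patients, the assumed 80% starting power and compound symmetry with ρ between 0.5 and 0.9. The documents do not show that patients will be lost, so shrinkage of the primary analysis cannot be stated as a fact of the plan. The case for change is consistency and tolerance of a missing block or region at low cost.

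**What to change.** In 3.7.1, analyse each SA1 metric with a linear mixed model:

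- fixed effects for condition, region and condition × region, with age and sex as covariates;
- random effects for patient and patient-by-condition, and patient-by-region if estimable;
- small-sample degrees of freedom;
- pairwise condition contrasts taken from this model, which would also replace the independent-samples t-tests, unsuited to conditions compared within patients.

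Keep the complete-case repeated-measures ANOVA as a sensitivity analysis. Report how many patients contribute to each contrast, and the number and cause of empty cells. BIS in 3.7.2 may use the same model for consistency, but needs it less.

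The cost is a change of wording and some modelling care; no new data are needed, and the model family is already planned for SA3. The downside is reliance on missing-at-random: the model does not correct bias if cells are empty because δ-waves were suppressed, which is why the causes need reporting.

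### SA1 names independent-samples t-tests, beside repeated-measures ANOVA, for conditions measured in the same 30 patients

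*Protocol article*

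**What the plan says.** Section 2.1.2 sets the design: "Using a within-subject study design, this study will enroll 30 neurologically healthy patients scheduled for elective surgery under GA". It gives no power calculation: "The sample size is justified based on feasibility, prior literature, and the within-subject design of the study".

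Section 2.2.2 gives each patient in-phase, anti-phase and sham "stimulation blocks for 3 min each, with 20-s pauses between each stimulation type (10 min total"). It adds that "no randomization of stimulation blocks will be conducted" and that in-phase comes first.

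Section 3.7.1 compares the δ-wave metrics across the three conditions "and cortical regions of interest (frontal, central, midline, parietal, temporal, occipital"), with "comparisons assessed using repeated-measures ANOVA and independent-samples" t-tests, and lists age and sex as covariates.

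Section 3.7.2 compares BIS over the same three blocks with "repeated-measures ANOVA and pairwise paired" t-tests and Holm–Bonferroni correction. Section 3.7.3 names linear mixed-effects analyses for the three pain epochs.

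**The concern.** Condition and region both vary within the patient, and section 3.7.1 defines no independent groups. An independent-samples t-test therefore has nothing in this comparison to which it properly applies. It also conflicts with the paired tests that the article uses for BIS on the same blocks.

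What is at stake is the pairwise part of SA1. The hypotheses in sections 1.8 and 4.1 are directional contrasts: in-phase against sham and anti-phase against sham. A three-level omnibus test shows only that some condition differs, so follow-up tests must carry those contrasts. By analogy with section 3.7.2, the t-tests are presumably meant for that. An unpaired version leaves between-patient variation, in a cohort aged 18 to 80, in the error term. The justification of 30 patients rests in part on removing that variation.

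**Working it through.** **Inputs from the article.** n = 30; all three conditions in every patient; tests as named in sections 3.7.1 and 3.7.2. The article gives no alpha, power, effect size, SD or within-patient correlation, so 30 cannot be reproduced as the result of a calculation.

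**Inputs assumed.** Two-sided 5% level; equal variance σ² in each block; one summary value per patient and block; within-patient correlation ρ varied; effect d in units of the between-patient SD.

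**Step 1: standard errors.** The mean difference between two blocks has true variance 2σ²(1 − ρ)/n. The independent-samples test estimates it as 2σ²/n. Its standard error is therefore too large by the factor 1/√(1 − ρ):

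- ρ = 0.3: 1/√0.7 = 1.20
- ρ = 0.5: 1/√0.5 = 1.41
- ρ = 0.7: 1/√0.3 = 1.83
- ρ = 0.8: 1/√0.2 = 2.24

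**Step 2: effect at which the paired test has 80% power.** With 29 degrees of freedom and the noncentral t distribution, 80% power needs a mean difference of about 0.53 SDs of the paired difference. That SD is σ√(2(1 − ρ)), so d = 0.529 × √(2(1 − ρ)). At ρ = 0.5 this is 0.529 × 1 = 0.529. At ρ = 0.8 it is 0.529 × 0.632 = 0.335.

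**Step 3: unpaired test on the same paired data.** 58 degrees of freedom, 40,000 simulated trials per setting:

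| ρ (assumed) | d | Paired power | Unpaired power | Unpaired type I error (nominal 5%) |
|---|---|---|---|---|
| 0 | 0.748 | 80% | 81% | 5.0% |
| 0.3 | 0.626 | 80% | 69% | 2.0% |
| 0.5 | 0.529 | 80% | 53% | 0.7% |
| 0.7 | 0.410 | 80% | 25% | 0.06% |
| 0.8 | 0.335 | 80% | 9% | about 0.01% |

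The loss is 80 − 69 = 11 points at ρ = 0.3, 27 points at 0.5, 55 at 0.7 and 71 at 0.8. It passes half of the 80% (40 points) between ρ = 0.5 and 0.7, at about 0.6.

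**Step 4: the same comparison at a fixed effect, d = 0.5.** Paired against unpaired power is 61% and 48% (ρ = 0.3), 75% and 47% (0.5), 93% and 47% (0.7), 99% and 46% (0.8). The unpaired test gains nothing from a higher correlation.

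**Step 5: covariates.** A t-test has no place for age and sex, so that part of the sentence can apply only to the ANOVA. Write a patient's value in block k as block effect + patient effect + (age and sex terms) + error. In the difference between two blocks, the age and sex terms cancel, because both are constant within the patient. As main effects they cannot reduce the error of a block contrast. They matter only if they are allowed to modify the block effect.

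**The case against.** The best defence is that the plan also names repeated-measures ANOVA, and names it first. That test keeps the pairing, and the article does not say which procedure is the decisive one for SA1. This stands: the omnibus test of condition is sound, and a reader who concluded that SA1 has no valid test would go beyond the text. It does not rescue the t-tests, because no between-patient comparison is described for which they could be meant. Section 3.7.2 shows that the authors use paired tests for these blocks, so a drafting slip is plausible. That makes the correction easy but leaves the stated test wrong. Nor is this detail left to an unseen analysis plan, since the article itself names the test.

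Three stronger readings are tempting, and the documents support none of them.

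- *Most of the power is lost.* That is so only above a correlation of about 0.6. High correlation is plausible for EEG amplitude within a patient, but the article gives no value.
- *The test inflates false positives because it treats single waves as independent.* Section 3.2 bases the primary analyses on individually detected waves, and section 3.7.1 segments each wave as one event. Yet the unit of the t-test is never stated, and section 3.7.1 refers to subject-level and group-level summaries. On patient-level values with positive correlation, the error is conservative.
- *Adding age distorts the block effect.* That would need an uncentred block-by-age interaction. Section 3.7.1 specifies neither an interaction nor a coding, and a plain age main effect leaves the block contrast unchanged.

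**Conclusion.** The point holds for the t-tests and not for the repeated-measures ANOVA. Section 3.7.1 names an unpaired test for within-patient comparisons, against the design in sections 2.1.2 and 2.2.2 and against the paired tests in section 3.7.2.

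The consequence is missed effects in the contrasts against sham: from 80% paired power down to about 69% at ρ = 0.3 and 9% at ρ = 0.8, with a true type I error of about 0.7% at ρ = 0.5. These figures assume patient-level values, equal variances, positive correlation and a two-sided 5% level. That the t-tests are the follow-up contrasts is an inference from the parallel with section 3.7.2. The covariate wording cannot be carried out for a t-test, and age and sex as main effects add no precision to a within-patient contrast.

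**What to change.** In section 3.7.1, replace the independent-samples t-tests with one of two options:

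- paired contrasts on patient-level block summaries, with Holm–Bonferroni correction as in section 3.7.2; or
- contrasts from a linear mixed model with block as a fixed effect and a patient random effect. State the random effect explicitly, because section 3.7.3 names mixed models without spelling it out.

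Do not add a period term. With one fixed block order, period and block coincide and cannot be estimated separately. If age and sex are kept, use them only as mean-centred modifiers of the block effect.

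The cost is one sentence and no new data. The choice should be settled before any condition results are seen.
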